## Abstract

**Background:**

Intimate partner violence (IPV) during or before pregnancy is associated with many adverse health outcomes. Pregnancy-related complications or poor infant health outcomes can arise from direct trauma as well as physiological effects of stress, both of which impact maternal health and fetal growth and development. Antenatal care can be a key entry point within the health system for many women, particularly in low-resource settings. Interventions to identify violence during pregnancy and offer women support and counselling may reduce the occurrence of violence and mitigate its consequences.

**Methods:**

Following a formative research phase, a randomized controlled trial will be conducted to test a nurse-led empowerment counselling intervention, originally developed for high-income settings and adapted for urban South Africa. The primary outcome is reduction of partner violence, and secondary outcomes include improvement in women’s mental health, safety and self-efficacy. The study aims to recruit 504 pregnant women from three antenatal clinics in Johannesburg who will be randomized to the nurse-led empowerment arm (two 30-min counselling sessions) or enhanced control condition (a referral list) to determine whether participants in the intervention arm have better outcomes as compared to the those in the control arm.

**Discussion:**

This research will provide much needed evidence on whether a short counselling intervention delivered by nurses is efficacious and feasible in low resource settings that have high prevalence of IPV and HIV.

**Trial registration:**

The study was registered in the South African Clinical Trials Registry (DOH-27-0414-4720) on 11 August 2014 and in the ISRCTN Registry (ISRCTN35969343) on 23 May 2016).

## Background

Violence against pregnant women is a global health concern. Studies have documented prevalence rates of partner violence during pregnancy ranging from 4–57 % globally [1–3]. South African studies estimate that 25–35 % of pregnant women experience past 12 month exposure to physical or sexual violence from a partner [4–6].

Intimate partner violence (IPV) during or around the time of pregnancy has been associated with many adverse health outcomes for the pregnant woman and her baby due to direct trauma, as well as physiological effects of stress from current or past violence that can impact fetal growth and development. Previous research has found that women experiencing violence during pregnancy had higher rates of intrauterine growth retardation and preterm labour [7–9], higher rates of miscarriage [10, 11], antepartum haemorrhage [12] and high blood pressure [13]. Violence during pregnancy has also been associated with maternal mortality [14] and perinatal, infant and child mortality [15, 16]. A recent systematic review and meta-analysis found that women reporting IPV in pregnancy were more likely to have a low birth weight infant and experience pre-term birth [17]. In addition, intimate partner violence has been associated with increased rates of HIV infection and HIV risk behaviour [18]. The maternal, infant, and reproductive health risks from intimate partner violence make it imperative that violence against women be more fully addressed during antenatal care.

Antenatal care can be a critical point of intervention for women suffering violence. Globally, 83 % of women have had at least one antenatal care visit [19], and even in low-resource settings women attending only one or a few antenatal care visits may benefit from an intervention which can be provided in a single session and can potentially reduce the occurrence of violence and mitigate its consequences. Other urgent health risks during pregnancy, such as HIV/AIDS, STI prevention, and malaria prophylaxis, are routinely addressed during antenatal care, however, identification and response to violence during pregnancy has not been routinely incorporated into antenatal care despite its potentially serious consequences and known adverse health outcomes. While the primary outcome of the study is to reduce partner violence, we also expect the intervention to have a positive impact on the mental health, safety and self-efficacy of participants.

Some health care providers understand how women's experiences of violence affect their health and the health of their infants, and many in South Africa and elsewhere have attempted to help their patients who are experiencing violence by a partner [20]. However, the evidence base is still limited for intervention strategies in the health sector and the antenatal care setting in particular. Two studies in high-income settings found significant positive results around a nurse-led antenatal intervention for IPV [21, 22]. Others found promising or insignificant results, although there was great variation in intensity and content of the intervention, and small sample sizes meant insufficient power to detect differences between groups [23].

While little evidence exists on effective interventions to identify and address violence in the health sector in low-resource settings, evidence from higher resource settings has shown some elements of promising interventions that could be adapted and replicated in other settings [24]. Empathetic listening is one of the most important elements of effective interventions to address violence. This, combined with discussions about safety planning and options for ending violence can be a valuable and empowering means of problem-solving and building self-efficacy in this context [21–23, 25, 26]. Some studies have found that having a focal person at the health centre who is specially trained on violence and dedicated to the issue can be an important element in responding to violence [27]; others identified support groups as a potentially positive intervention option [28]. In general, research has confirmed the value of interventions to address partner violence in antenatal care settings and suggests that even a single counselling session can result in improved safety behaviours and reduced levels of intimate partner violence [21, 22].

South Africa is an ideal setting to test such an intervention because of the high rates of antenatal care attendance. More than 92 % of women have at least one antenatal care visit and deliver with a skilled attendant [29]. In addition, South Africa has a high burden of HIV [30] and women with HIV are primarily identified in antenatal care. Violence against women and gender inequality are closely linked with HIV risk through several mechanisms. Violence or the threat of violence can limit HIV prevention behaviours, and disclosure of HIV status can provoke partner violence [31]. Therefore, it is critical that interventions to address violence against women in antenatal care are linked with HIV counselling and testing in South Africa as this study does.

## Methods/Design

A randomized controlled trial (RCT) of a two-session empowerment counselling intervention among pregnant women (*n* = 504) experiencing past-year physical and/or sexual IPV will be carried out at three antenatal clinics in Johannesburg, South Africa. Individual women will be randomized to the intervention or control group, with women in the intervention group receiving the empowerment counselling intervention and women in the control group receiving enhanced standard of care in the form of a list of referrals to local resources.

### Objectives

The project aims to achieve the following objectives:To test a nurse-led counselling intervention for abused pregnant women receiving antenatal care in South Africa that could be incorporated into the routine antenatal care package.To determine whether the counselling intervention being tested during pregnancy can reduce the recurrence of intimate partner violence and the frequency and severity of this violence.To determine whether the counselling intervention being tested is effective in improving safety, empowerment, mental health, and help- and health-seeking behaviour of abused pregnant women.To assess whether, at baseline, women experiencing intimate partner violence differ from women who do not experience intimate partner violence in regard to mental health, self-efficacy, and HIV risk behaviours.To assess whether HIV-positive women who have experienced intimate partner violence differ from HIV-positive women who have not experienced intimate partner violence with regard to PMTCT uptake and adherence as measured at follow up.

The design of the randomized controlled trial was adapted following a formative research stage described elsewhere [32, 33], which included an assessment of the current response to violence against women in both the public and private sectors. Findings from the formative research validated the importance of having an appropriate response to violence against women in the clinic setting, and informants (providers and pregnant women) were supportive of the proposed intervention research [33]. The formative stage included identification of the organizations that respond to the health and psychosocial needs of women experiencing violence; examination of the current initiatives to address violence against women; assessment of the technical capacity of health workers to address violence and the barriers to implementation of a health sector response at present.

To avoid disclosing the nature of the research and to emphasize the focus on keeping women “safe” during pregnancy and the postpartum period, the study was named “Safe & Sound.”

The randomized controlled trial (RCT) will test the efficacy of an intervention to address partner violence during pregnancy. Women screening positive for violence and who satisfy the eligibility criteria will be randomized to the intervention or control group (Fig. 1). The intervention group will receive up to two sessions of a counselling intervention and both groups will receive a brief information sheet with local referrals, including for counselling, shelters, legal resources, child protection services, police, and other relevant NGOs. Each of the listed referrals was contacted and its willingness and capacity to respond to referrals during the course of this study was assessed. Selected agencies will be included as active referral options. The protocol complies with the guidelines of the Standard Protocol Items: Recommendations for Interventional Trials (SPIRIT), and all data collection is in compliance with Consolidated Standards of Reporting Trials (CONSORT) guidelines.

**Fig. 1 Fig1:**
[figure not shown]
Study design provides a visual depiction of the study design

At enrolment, data will be collected on socio-demographic characteristics of participants, including age, number of children, relationship and employment status, education level, housing type, length of stay in Johannesburg, socio-economic status and hunger index, country of origin, as well as number of pregnancies and live births for descriptive purposes and for potential inclusion in adjusted analyses.

### Primary outcome

Intimate partner violence will be measured using a modified version of the WHO instrument from the WHO Multi-Country Study on Women’s Health and Domestic Violence against Women [34]. This instrument assesses women’s experience of physical, sexual, and emotional violence as well as controlling behaviours by a male intimate partner. The effect of the intervention on the primary outcome of physical and/or sexual intimate partner violence will be assessed by comparing the percentage of women in the intervention vs. control groups reporting acts of physical and/or sexual partner violence during the study period and by analysing the patterns of frequency and intensity of the violence between the two study groups based on follow up data.

### Secondary outcomes

The two study arms will be compared on a number of secondary outcomes measured at follow-up, including mental health, safety planning, community resource use, and self-efficacy. The Hospital Anxiety and Depression Scale (HADS), a 21 question standardized instrument measuring anxiety and depression, will be used to assess the effect of the intervention on these mental health outcomes [35]. A score of 8 or above is considered clinically significant. An adapted version of the Safety Behavior Checklist [36] will be used to calculate an average score of safety behaviours used in the event of escalating violence. These include actions such as keeping an identity card available, keeping a bag packed in case of escalating violence, and removing knives or weapons from the home. Self-efficacy will be measured using the General Self-Efficacy Scale [37] and includes a set of questions on beliefs and actions indicating feelings of personal control over one’s life. Uptake of community resources, particularly those included on the study referral sheet, will also be assessed as a secondary study outcome by comparing scores between study arms.

### Sub-study outcomes

Two sub-studies will be linked to the RCT. One will assess the role of IPV on the uptake and adherence to prevention of mother-to-child transmission (PMTCT) among HIV-positive women. This sub-study will compare HIV-related outcomes in two groups of HIV-positive women: IPV-positive women in the control group and IPV-negative women who will be followed up for the purposes of this sub-study. Adherence to antiretroviral therapy among HIV-positive participants will be measured using the 30-day Visual Analog Scale (VAS). The VAS has been validated in South Africa [38], and ‘good adherence’ will be analysed using a cut-off of >95 % adherence. To further assess PMTCT, self-report questions will be adapted from a recent study among pregnant women in Cape Town, South Africa [39]. Each step in the PMTCT cascade will be analysed as a dichotomous variable (completed step vs. not completed).

A second sub-study will compare at baseline socio-demographic characteristics and mental health status of women experiencing intimate partner violence to those not experiencing partner violence to assess the role of IPV status on women’s mental health prior to enrolment in the study. These baseline measures will include post-traumatic stress (using the Harvard Trauma Questionnaire (HTQ) [40], anxiety and depression status, and selected socio-demographic characteristics. In addition, the association between IPV and selected socio-demographic characteristics will be assessed to determine which characteristics are associated with IPV independent of the intervention.

### Recruitment and randomization

Pregnant women will be screened for eligibility. Those who are at least 18 years old and less than 33 weeks gestation (to allow enough time for the second intervention session) and who are able to communicate in one of the most common local languages (English, Sotho, or Zulu) will be eligible to participate in the randomized controlled trial. Potential participants will also be asked if they have experienced any of a number of forms of partner violence in the past 12 months. Only those reporting that they have experienced physical or sexual violence by their current or most recent partner in the past 12 months will be eligible. Prior to being enrolled, women will also be screened for immediate safety risk. Reported risk of imminent lethal violence by a partner, fear that a child in the home is at immediate risk of lethal violence by the partner, and being at suicidal risk (as determined by having ideation with a plan to commit suicide) will result in an immediate referral and disqualify women from participating.

Women will be recruited during their routine antenatal appointments at primary healthcare clinics in urban Johannesburg. All clinics are part of the district public health service and generally serve very low income communities. The study will be introduced by a research nurse, who will provide a group introduction to the study without identifying the study as being related to violence but rather framing it as a study on women’s health during pregnancy. A study flier will be distributed with the name of the study and a phone number and first name of the research nurse assigned to that clinic site. Interested women will be offered an opportunity to speak to nurses following their routine clinic care or to schedule an appointment for another time.

Randomization will be conducted through block randomization procedures with study arm assignment revealed upon opening of sequential opaque sealed envelopes prepared in Geneva by the Department of Reproductive Health and Research, World Health Organization. Study nurses will not be blinded to study arm; the same nurse who conducts the baseline interview will also randomize eligible participants.

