## Discussion

The results of this study will provide much needed evidence on how to address the needs of abused women in an antenatal care package and on how to implement an appropriate health sector response to violence against women in low-resource settings. Testing an intervention under controlled conditions to determine efficacy is an important step prior to integrating it into a clinic setting and determining how to implement it effectively. This study is designed to test the efficacy of an intervention and as such, dedicated research nurses will be hired and trained to carry out the research aspects (e.g., determining eligibility, collecting data, randomizing eligible participants) as well as the clinical aspects of implementing the intervention or control conditions.

Several limitations should be noted. The overlapping roles of research nurses in managing the research and intervention aspects and the lack of blinding of study nurses are important limitations in the study design. Since nurses are trained in how to implement the intervention it will potentially be difficult or professionally distressing for them to maintain a control condition throughout the study. This will be addressed thoroughly in the training and team meetings.

It was decided that for ethical reasons the control group would receive enhanced standard of care, a referral services list, rather than receiving standard level of care, which in South Africa is presently nothing at all. Women in the study may benefit from the referral list as well as from the baseline encounter with the nurse in which she inquires about her experiences of violence in a kind, non-judgmental way. Inquiring about violence exposure in the context of research may lead women to contemplate the role of violence in their lives, which could increase their awareness and recognition of the problem and potentially influence outcomes [48]. These conditions may reduce the relative difference in outcomes between the intervention and control groups and could bias results towards the null hypothesis. These limitations will be monitored during the study through the process evaluation and regular study monitoring to understand their influence on the study outcomes.

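### The nurse who decides eligibility also opens the block-randomized envelopes and delivers both arms, so enrolment and allocation are not separated and some allocations may be predictable

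*Protocol article*

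**What the plan says.** Protocol article, Recruitment and randomization: "Randomization will be conducted through block randomization procedures with study arm assignment revealed upon opening of sequential opaque sealed envelopes", with the envelopes "prepared in Geneva by the Department of Reproductive Health and Research, World Health Organization". The same paragraph adds that "Study nurses will not be blinded to study arm" and that "the same nurse who conducts the baseline interview will also randomize eligible participants". The section also refers to a research nurse assigned to each clinic site.

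Protocol article, Discussion: the dedicated research nurses are responsible for "determining eligibility, collecting data, randomizing eligible participants" "as well as the clinical aspects of implementing the intervention or control conditions". The Discussion lists the overlapping roles and the lack of blinding as limitations. It also says of the nurses that "it will potentially be difficult or professionally distressing for them to maintain a control condition throughout the study", and answers this with training and team meetings.

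Data management: the data manager compares screening logs with case report forms. Forms and logs are checked visually in full, and files are reviewed at monitoring visits.

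The suicidality exclusion is worded in two ways. Recruitment and randomization requires ideation together with a plan. The danger-evaluation element under The intervention excludes a woman who discloses suicidal ideation, with no mention of a plan.

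The article does not state the block length, whether it is fixed or varied, whether nurses know it, or whether each clinic has its own run of envelopes.

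**The concern.** Allocation concealment requires that whoever decides on entry cannot tell what the next allocation will be. Opaque, sequential envelopes prepared off site hide the next card. They do not stop inference from cards already opened, and in a blocked sequence past cards carry information about the next one. Here the person assessing entry is unblinded, opens the envelopes and delivers the arms, so she learns past allocations in the ordinary course of her work.

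The listed safeguards do not address this. The comparison of screening logs with case report forms sets one nurse-made record against another, so a decision not to enrol would look the same in both. Training and team meetings are aimed at keeping intervention content out of the control arm.

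If entry decisions were influenced by a foreseen arm, the arms would differ at baseline in ways that may predict later violence. Intention-to-treat analysis preserves the groups as randomized. It cannot repair groups already selected at entry. The enrolment characteristics listed for possible adjustment are socio-demographic and obstetric, not severity of violence. The two wordings of the suicidality exclusion leave the nurse some discretion over who is eligible.

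**Working it through.** The article gives no figure for block length or predictability, so there is none to reproduce. The only input taken from it is the sample size, 252 × 2 = 504 (Sample size). Everything else is a scenario, with 1:1 allocation assumed.

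**Certain allocations, fixed block of 2m, one run per clinic, block length known or inferred.** Once one arm is used up within a block, the rest of the block is known. The expected length of that final stretch is 2m/(m+1), so the certain share is 1/(m+1). Check for a block of 4: the six orderings AABB, ABAB, ABBA and their mirror images end in known stretches of 2, 1 and 1. The mean is 4/3, and (4/3)/4 = 33.3%.

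- Block of 4: 1/3 = 33.3%; 504/3 = 168
- Block of 6: 1/4 = 25%; 504/4 = 126
- Block of 8: 1/5 = 20%; 504/5 = about 101

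**Other schemes, by simulation.** In the varied-block rows the nurse is assumed to know which lengths are possible. In the shared-sequence rows each nurse sees about one third of allocations and can tell where each block starts.

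| Assumed scheme | Certain in advance | Best guess correct (chance 50%) |
|---|---|---|
| Fixed 4 / 6 / 8, run per clinic | 33.3% / 25% / 20% | 71% / 68% / 67% |
| Varied 4 and 6, run per clinic | 5.6% | 69% |
| Varied 4, 6 and 8, run per clinic | 2.2% | 68% |
| Varied 2, 4 and 6, run per clinic | 4.1% | 70% |
| One sequence over 3 clinics, fixed 4 / 6 / 8 | 3.7% / 0.9% / 0.3% | 57% / 56% / 55% |

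**What the last column adds.** The best guess is the arm that is behind in the running count. Every complete block ends level, so within a run that the nurse sees in full this rule needs no knowledge of block length. For lengths 4 and 6 mixed, weighting by length gives (4 × 70.8% + 6 × 68.3%)/10 = 69.3%, against 69.2% simulated. Varying the lengths therefore removes most of the certainty but little of the better-than-chance guessing.

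**Illustration of size (assumptions only, not an estimate).** Suppose steering acts on a quarter of the certain allocations, and women steered to one arm differ by 20 percentage points in recurrence risk from those steered to the other. The spurious difference between arms is certain share × 0.25 × 20 points:

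- Fixed block of 4: 0.333 × 0.25 × 20 = 1.7 points
- Fixed block of 8: 0.20 × 0.25 × 20 = 1.0 point
- Varied blocks: 0.022 to 0.056 × 0.25 × 20 = 0.1 to 0.3 points
- Shared sequence: at most 0.037 × 0.25 × 20 = 0.2 points

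The difference on which the sample size is based is 7%.

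**The case against.** The strongest reply is that the article fixes only the word block. Lengths, their variation and any stratification are commonly left to the full protocol and often withheld from sites on purpose, so their absence from an article is no fault. That stands. It rules out the stronger reading that the nurses can foresee many allocations, or that 101 to 168 of the 504 are exposed. Those counts need small, fixed, inferable blocks run per clinic, and the article states none of these.

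Other inferences that a reader might draw are also not supported:

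- **Nurses can time enrolment by rescheduling.** The later appointment is an option offered to interested women after a group introduction, before individual screening. No deferral after disclosure of violence is described.
- **The exclusions are a matter of the nurse's judgement.** They rest largely on what the woman reports. Some discretion remains, because lethal risk has no stated threshold and suicidality has two wordings.
- **The nurses have a stated motive to steer.** The sentence on distress concerns maintaining the control condition, not choosing whom to enrol.
- **One nurse sees every allocation at her site.** A nurse is assigned to each site, but the article does not say that she alone handles a whole run.

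Opportunity is also limited. With one to five women screened per session and 25% expected to report violence, a session yields 0.25 to 1.25 such women, so there will seldom be several to match to envelopes. The article openly lists the overlapping roles as a limitation.

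None of this removes the overlap itself, which is a stated design choice, and naming a limitation does not reduce it.

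**Conclusion.** The point holds as a weakness in allocation concealment of unknown size. It is established that unblinded nurses assess eligibility, interview, open the envelopes of a blocked sequence and deliver both arms, and that none of the described checks would reveal selective entry. How many allocations could be predicted is not established. The certain share runs from 20–33% (fixed blocks of 4 to 8 per clinic) down to about 2–6% (varied blocks) or under 4% (one shared sequence). Nothing in the article shows that steering is expected or likely. The procedure should be changed because a better one is cheap and any bias introduced at entry could not be undone in the analysis.

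**What to change.** **Lock enrolment before the arm is revealed.** The nurse records eligibility, the danger screen and the baseline case report form as complete. She then phones or texts the participant number to the existing data manager, who logs it and releases the next allocation from the list prepared in Geneva.

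**If envelopes stay,** write the participant number, date and time on the sealed envelope before opening it. Have the data manager reconcile envelope order with the screening log at the checks already planned.

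**In either case,** use randomly varied block lengths not disclosed to the nurses, or state that this is already done. Remote release alone is not enough, because the nurses deliver the arms and so learn past allocations anyway. Some better-than-chance guessing will remain with a separate run per clinic. A single list across the three clinics would lower it, at the price of looser balance within each clinic.

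**Reconcile the two wordings of the suicidality exclusion** in Recruitment and randomization and The intervention, so that eligibility does not depend on which one the nurse applies.

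Cost: a new or confirmed list, and a short wait or a little extra logging per randomized woman. The article gives the data manager checking duties only, so availability for real-time release must be confirmed, with logged sealed envelopes as a back-up.
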